Self-care refers to the ability of individuals, families, and communities to take intentional and purposeful actions to promote and maintain their health, prevent illness, and manage disease and disability, with or without the support of healthcare providers [12]. Effective techniques for enhancing self-care behaviors in women are organized into three categories: lifestyle modification, preventive behaviors and screening, and disease and treatment management behaviors. Self-care behaviors that help prevent HPV infection include undergoing Pap smears, vaccination, consistent and correct use of condoms during sexual intercourse, and limiting sexual partners to one [11,12]. Self-care interventions are among the most important and promising approaches to improving universal health coverage and well-being, both for health systems and individuals. As accessible, cost-effective, and acceptable interventions, they promote self-efficacy, independence, and participation in health [13], yet nearly four billion women of reproductive age worldwide lack access to such services [14].

One of the most widely used theories in health behavior is the Health Belief Model (HBM), which has extensive applications in health education for various health-related issues. The HBM posits that six constructs predict health behavior: perceived susceptibility, perceived severity, perceived benefits, perceived barriers, self-efficacy, and cues to action [15]. A study by Bayrami et al. (2019) aimed to assess the constructs of the HBM in relation to the willingness to receive HPV vaccination among female students at Urmia University of Medical Sciences. According to the results, perceived susceptibility, perceived severity, perceived benefits, perceived barriers, self-efficacy, and cues to action were all significantly associated with the acceptance of the HPV vaccine [16].

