***Inclusion Criteria***

- - Positive HPV-DNA test
  - Iranian nationality
  - Married
  - Age between 15 and 49 years
  - Literacy (ability to read and write)
  - No chronic psychiatric disorders
  - No known malignant diseases
  - No previous participation in educational or counseling sessions related to STIs

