***Exclusion Criteria***

- - Absence from more than two educational sessions
  - Incomplete or incorrect completion of the questionnaire
  - Lack of willingness to continue participating in the study

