**Table 1. Health Belief Model-Based Educational Intervention**

| **Session** | **Main Objective** | **Educational Content** | **Teaching Methods and Schedule** |
| --- | --- | --- | --- |
| First | Improve awareness about HPV and sexual self-care | PowerPoint presentation, Session 1 handout | 1) Introduction of the facilitator and participants, study objectives (10 min) 2) Information on HPV, its global and local prevalence, and the importance of sexual self-care (40 min) 3) Q&A session (10 min) |
| Second | Impact on perceived susceptibility, perceived severity, and perceived benefits of the Health Belief Model | PowerPoint presentation, Session 2 handout | 1) Review of the previous session (5 min) 2) Explanation of the consequences of not having a Pap smear test, non-vaccination against non-infecting strains, effects on marital life and quality of life, issues with having multiple sexual partners (45 min) 3) Q&A session to address perceived benefits (10 min) |
| Third | Impact on perceived barriers and self-efficacy of the Health Belief Model | PowerPoint presentation, Session 3 handout, Educational video | 1) Review of previous sessions (5 min) 2) Request women with HPV to share their issues since the onset of symptoms or diagnosis, discuss the concept of sexual self-care and its connection to self-efficacy (40 min) 3) Share common experiences and solutions with each other, summarize the taught materials using the educational video (15 min) 4) Q&A session (10 min) |
| Fourth | Impact on cues to action and performance of the Health Belief Model | PowerPoint presentation, Session 4 handout, Educational video, Role-playing | 1) Review of previous sessions (5 min) 2) Teach various sources of information about HPV (15 min) 3) Ask women to express their fears about symptoms and provide self-care recommendations, advise appropriate behaviors, and communicate problems and needs to healthcare providers (30 min) 4) Role-playing, educational video, and summarization of the taught materials (10 min) 5) Q&A session (10 min) |

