***Study instruments***

The three study instruments are explained in what follows.

**-****Demographic and obstetric information questionnaire**: It consists of 16 questions including: Age, Spouse's Age, Education Level, Spouse's Education Level, Employment Status, Spouse's Occupation, Income Level, Duration of Marriage, Number of Pregnancies, Number of Deliveries, Type of Delivery, Number of Abortions, Contraceptive Method, History of Pap Smear, History of HPV Vaccination, Duration of HPV Infection Based on Diagnostic Tests.

-**The Sexual Self-Care in Women of Reproductive Age (****FSHS) questionnaire**: It consists of 40 items scored on a 5-point Likert scale ranging from Never (1) to Always (5) across 4 domains: prevention of sexually transmitted infections (STIs), prevention of gynecological cancers, prevention of unintended pregnancies, and promotion of sexual health. Developed using a deductive approach based on the Waltz model in 2021 by Yazdani and colleagues in Iran, the tool has demonstrated a content validity index (CVI) of 0.93, a content validity ratio (CVR) of 0.96, and a high internal consistency reliability with a Cronbach's alpha of 0.94. The stability of the instrument, measured by intra-cluster correlation, was 0.97 (confidence interval: 0.94-0.98), indicating strong validity and reliability in the Iranian population, making it a suitable measure of sexual self-care [24].

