**Table 2. Researcher-Designed Questionnaire Based on the Health Belief Model**

| **Question Type** | **Questions** | **Scale** |
| --- | --- | --- |
| Perceived Susceptibility | 1. I am at risk of complications from HPV. 2. I am at risk of cervical cancer. 3. I am at risk of high-risk HPV strains. 4. My partner is at risk of the disease. | 5-point Likert scale (1=Strongly disagree, 5=Strongly agree) |
| Perceived Severity | 1. The disease causes problems in sexual relations. 2. Thinking about the complications of HPV scares me. 3. Thinking about the problems caused by HPV infection makes me anxious and worried. 4. If I experience HPV complications, my spouse and family will blame me. 5. The cost of treatment is high. 6. Quality of life decreases after contracting the disease. | 5-point Likert scale (1=Strongly disagree, 5=Strongly agree) |
| Perceived Benefits | 1. Women who engage in sexual self-care experience fewer physical and emotional crises. 2. Sexual self-care reduces the costs associated with cervical cancer. 3. Sexual self-care prevents my partner from contracting the disease. 4. Sexual self-care allows me to enjoy sexual relations more. 5. Sexual self-care helps prevent high-risk HPV strains. | 5-point Likert scale (1=Strongly disagree, 5=Strongly agree) |
| Perceived Barriers | 1. I don't have enough time to get the HPV vaccine. 2. I don't have enough time to visit a doctor or midwife. 3. I can't afford the HPV vaccine. 4. I don't have access to accurate information about sexual self-care. 5. My partner agrees to use condoms during sexual relations. 6. I feel embarrassed about vaginal exams and Pap smears. 7. I am afraid of vaginal exams and Pap smears. 8. Fear of side effects from the HPV vaccine prevents me from getting it. | 5-point Likert scale (1=Strongly disagree, 5=Strongly agree) |
| Self-Efficacy | 1. Reading brochures and using educational videos are effective for sexual self-care. 2. Media (TV and social media) are effective for sexual self-care. 3. My doctor and midwife assist me with sexual self-care. | 5-point Likert scale (1=Strongly disagree, 5=Strongly agree) |

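### Barrier items 1, 3 and 8 give an already vaccinated woman no marked response, so her barrier score is ambiguous and a blank could also cost her primary outcome data

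*Protocol*

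**What the plan says.** **Eligibility.** The Inclusion Criteria require a "Positive HPV-DNA test". The only criterion on prior exposure is "No previous participation in educational or counseling sessions related to STIs", and nothing restricts earlier vaccination. The demographic form (Study instruments) records "History of HPV Vaccination", so the plan itself allows for this status to vary.

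**Education.** The Background counts vaccination among the self-care behaviours: "undergoing Pap smears, vaccination, consistent and correct use of condoms during sexual intercourse". Session 2 in Table 1 covers the consequences of "non-vaccination against non-infecting strains".

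**Questionnaire.** Three of the eight perceived-barrier items in Table 2 concern getting the vaccine. Item 1 is about time ("I don't have enough time to get the HPV vaccine"), item 3 is about cost, and item 8 is about fear ("Fear of side effects from the HPV vaccine prevents me from getting it"). All are rated 1 to 5 by agreement. Table 2 shows no not-applicable response and no skip.

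**Removal.** The Exclusion Criteria list "Incomplete or incorrect completion of the questionnaire" without defining incomplete. Data management and analysis makes every analysis per protocol.

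**Role and status.** Perceived barriers are part of the secondary outcome (Outcomes; secondary objective 2). The questionnaire has still to go through expert content review, with revisions, and a face-validity check in 10 women (Study instruments).

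**The concern.** A vaccinated woman is asked what keeps her from something she has already done. Item 8 is the clearest case, because its wording assumes she has not had the vaccine. She could disagree strongly, choose the midpoint because the question does not concern her, or skip it. The protocol does not say which to expect or how to score it, so two women with the same views can get different barrier scores.

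Two things are at stake. First, a between-group difference in barriers at follow-up may partly show a difference in vaccination status. This also touches the Discussion's stated aim of finding which construct of the model matters most. Second, a questionnaire with blanks may be treated as incomplete. Under a per-protocol-only analysis, a problem in a secondary subscale could then remove a woman's FSHS data as well. If the teaching prompts vaccination, that loss could fall unevenly between the arms.

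**Working it through.** **The plan's own figures.** The claim disputes no stated number, but the sample size sets the scale for any loss. With the protocol's rounded z values, n = 2 × (1.96 + 0.84)² / 0.7² = 2 × 7.84 / 0.49 = 32.0 per group, which matches the stated 32. Dividing by 0.9 for dropout gives 35.6, against the stated 35. (The printed formula puts the 2 inside the square; that is a separate matter.) At 35 per group and d = 0.7, power by the normal approximation is 0.834.

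**Share of the barrier score.** The protocol states no scoring rule, so a simple sum is assumed.
- Full scale: 8 items × (5 − 1) = 32 points of range (8 to 40).
- Items 1, 3 and 8: 3 × 4 = 12 points.
- Share: 12 / 32 = 37.5%.
- Remaining five items (2, 4, 5, 6, 7): 5 to 25.

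**Effect of the ambiguity on one woman.** Suppose she answers 1 on all three items where she would otherwise have answered 3 or 4.
- From 3: 3 × (3 − 1) = 6 points, or 6/32 = 19% of the range.
- From 4: 3 × (4 − 1) = 9 points, or 9/32 = 28% of the range.

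**Effect on an arm mean.** The share of such women is not in the protocol; 10% to 30% is assumed.

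| Share of arm | Shift if from 3 | Shift if from 4 |
|---|---|---|
| 10% | 0.10 × 6 = 0.6 | 0.10 × 9 = 0.9 |
| 20% | 0.20 × 6 = 1.2 | 0.20 × 9 = 1.8 |
| 30% | 0.30 × 6 = 1.8 | 0.30 × 9 = 2.7 |

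**If blanks led to removal.** Suppose 10%, 20% or 30% of the intervention arm were removed and no controls (assumption). That is 3.5, 7 or 10.5 of 35 women.

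| Removed, intervention arm only | Power, d = 0.7 | Power with 10% dropout in both arms as well |
|---|---|---|
| none | 0.834 | 0.793 |
| 10% | 0.813 | 0.772 |
| 20% | 0.788 | 0.745 |
| 30% | 0.757 | 0.713 |

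The loss of power is modest. Bias would matter more, because the missing women would be selected by arm and by response to the teaching.

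**When the loss could differ by arm.** Figure 2 places the baseline questionnaires at enrolment, before allocation. Women vaccinated before entry should therefore be balanced by randomisation in expectation. Only vaccination after allocation can produce an arm-related loss. The window from session 2 to the last questionnaire is about 10 weeks: two further weekly sessions, then 8 weeks.

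**Would a mean of applicable items solve it?** Take a woman who rates the three vaccine items 1 and the other five 3. Before vaccination her mean is (3 × 1 + 5 × 3) / 8 = 18/8 = 2.25. After vaccination, with unchanged views and the three items dropped, it is 15/5 = 3.0. Her barriers appear to rise although nothing got worse, so this scoring should be avoided.

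**The case against.** The strongest reply is that a vaccinated woman does have a sensible answer. She can strongly disagree that time, cost or fear keeps her from the vaccine, and this reads naturally as no remaining vaccine barrier. If education leads to vaccination and her ratings fall, that is close to the effect the hypothesis seeks. This stands. A reader might infer that the barrier score is invalid for vaccinated women, and the documents do not support that. They support ambiguity, because nothing tells her to answer low and not at the midpoint or with a blank.

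A reader might also infer that women for whom the teaching worked will be removed from the trial. That needs vaccination within about 10 weeks, blanks in place of disagreement, and staff who treat those blanks as incomplete. The protocol establishes none of these, and absence and withdrawal are other routes to exclusion. Removal is a possibility left open by an undefined rule, not a predicted result.

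The effect on the primary outcome also arises from the exclusion rule and the per-protocol-only analysis, which form a wider problem than these three items.

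Finally, scoring may be left to an analysis plan, and the planned review may improve the wording. But the response options and the exclusion rule are set here, and no analysis plan can recover an answer women were not offered. The review covers essentiality, relevance and clarity. Nothing directs it to whether an item applies to a vaccinated woman.

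**Conclusion.** The point holds in a limited form. Vaccinated women are eligible and vaccination is taught, yet 3 of 8 barrier items are worded for an unvaccinated woman and offer no response for one already vaccinated. Her answers are ambiguous, and the barrier score partly measures vaccination status. The items carry 12 of 32 points if the score is a simple sum.

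Under the assumed shares of 10% to 30%, and answers of 1 in place of 3 or 4, an arm mean would move by 0.6 to 2.7 points. The true share vaccinated, at entry or during the trial, is unknown. The route to lost FSHS data is real but conditional on blanks being judged incomplete, and it differs by arm only through vaccination after allocation. The matter concerns a secondary subscale that is still open to revision, so it is modest in weight and worth correcting because the correction costs so little.

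**What to change.** Make these changes during the planned questionnaire review:

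1. Ask vaccination status at every questionnaire wave, not only at baseline.
2. Add an 'already vaccinated' response to barrier items 1, 3 and 8.
3. State in the Exclusion Criteria that this response, or a blank on these three items from a vaccinated woman, is not incomplete completion and removes her from no analysis.
4. Fix in advance how the response counts in the eight-item score, for example as the lowest category, meaning no remaining vaccine barrier. Do not use a mean of applicable items, because its composition would change with vaccination after randomisation.
5. Report items 2, 4, 5, 6 and 7 as a supportive score with the same composition for all women. Reverse-score item 5, which is worded as a partner's agreement to condom use and so runs opposite to a barrier.

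The cost is one extra question per wave, a few sentences of text, and one supportive analysis on a shorter scale. That shorter score leaves out vaccine barriers altogether, so it should stand beside the full score and not replace it. Eligibility and the content of the education do not change.

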***Data management and analysis***

Descriptive analysis will be used to report baseline characteristics. For continuous variables with a normal distribution, ANOVA will be used between subjects, and for continuous variables without a normal distribution, the Friedman test will be employed. The effectiveness of the intervention will be evaluated using ANOVA, and the impact of demographic variables on sexual self-care will be determined using logistic regression modeling. All statistical analyses will be performed using SPSS version 24. All statistical analyses will be performed using the per protocol analysis and at a significance level of less than 0.05.

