**Abstract**

**Background:** The human papillomavirus (HPV) is the most common sexually transmitted infection worldwide. The present study aims to examine the impact of an educational intervention based on the Health Belief Model (HBM) on sexual self-care among women of reproductive age infected with HPV.

**Method:** This is a randomized controlled trial with two parallel groups. Seventy women with HPV will be selected through simple random sampling from Arash Women's Comprehensive Hospital and Imam Khomeini Hospital in Tehran, Iran and will be allocated to a control group (n = 35) and an intervention group (n = 35). Participants in the intervention group will receive HBM-based sexual self-care education in four 45-60 min weekly sessions which will be held using the lectures, group discussions, question & answer sessions, PowerPoint presentations, pamphlets, educational videos, and role-playing. Data will be collected through a Demographic and obstetric information questionnaire, The Sexual Self-Care and HBM questionnaires, and will be analyzed through the ANOVA, Friedman test, and logistic regression modeling. All statistical analyses will be performed using SPSS version 24.

**Discussion:** Upon completion of this study, an increase in sexual self-care scores may indicate the effectiveness of this educational intervention. If proven effective, it can be recommended as a cost-effective method to achieve this goal, and it can be utilized by health professionals, including midwives and counselors to enhance sexual self-care among these women.

**Key-words:** Sexual Self-Care, Human Papillomavirus, Women, Health Belief Model, Intervention, Clinical trial

**Ethical code:** IR.TUMS.FNM.REC.1402.186

**Trial registration:** This study was registered in the Iranian Registry of Clinical Trials on 2024/01/01 (code: IRCT20231223060503N1)

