According to the results of a qualitative study conducted in Iran (2023), most women infected with HPV lacked sufficient knowledge about the virus, including its causes, symptoms, complications, prevention, and screening methods. Education, counseling, support, and healthcare services were identified as the main needs and challenges in reproductive and sexual health [17]. Based on the literature review, most studies have focused on the prevention of HPV infection. However, individuals who are already affected by this condition face numerous challenges, highlighting the need for further research into self-care practices for this group of patients. Given the Iranian and Islamic cultural context, HPV infection may be associated with negative psychological effects and significant challenges for Iranian women due to its sexual nature and the stigma attached to it, complicating efforts to educate, support, and address their needs [18,19]. Therefore, the present study aims to examine the impact of an educational intervention based on the Health Belief Model on sexual self-care among women of reproductive age infected with HPV.

**Hypothesis:** The educational intervention based on the Health Belief Model will lead to changes in perceived susceptibility, severity, benefits, barriers, and self-efficacy among women with HPV. These changes will, in turn, modify individual behavior and enhance sexual self-care in those affected by this disease.

**Objectives:** The primary objective of this study is to evaluate the effectiveness of an educational intervention based on the Health Belief Model on sexual self-care among women infected with the HPV. The secondary objectives of the study are:

1. To determine and compare the sexual self-care scores among women with HPV in the intervention and control groups before, immediately after, and 8 weeks following the intervention.
2. To determine and compare the items of the Health Belief Model (perceived susceptibility, perceived severity, perceived benefits, perceived barriers, cues to action, and self-efficacy) regarding sexual self-care among women with HPV in the intervention and control groups before, immediately after, and 8 weeks following the intervention.

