***Outcomes***

The primary outcome of the study is sexual self-care which will be measured through the sexual self-care in women of reproductive age (FSHS) questionnaire. The secondary outcome of the study will be participants’ perceived Susceptibility, severity, benefits, barriers, and self-efficacy regarding sexual self-care which will be measured through the researcher-designed questionnaire based on the HBM.

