**Discussion**

This randomized controlled trial will assess the impact of an educational intervention based on the HBM on sexual self-care among women of reproductive age infected with HPV.

Most HPV-related diseases can be prevented through education, screening programs, and vaccination [1]. Therefore, a well-designed, targeted educational program is crucial for promoting and maintaining sexual self-care among women, preventing disease, and managing illness and disability. Given the Iranian and Islamic cultural context, women affected by HPV may face significant psychological challenges and stigma due to the sexual nature of the virus, which can hinder their ability to receive education, support, and appropriate care [18, 19]. A qualitative study in Iran (2023) found that most women with HPV lacked sufficient knowledge about the virus, its causes, symptoms, complications, prevention, and screening methods. Moreover, education, counseling, support, and healthcare services were identified as key needs and challenges in reproductive and sexual health [17].

Upon completion of this study, an increase in sexual self-care scores may indicate the effectiveness of this educational intervention. If proven effective, it will contribute to the development of programs aimed at improving sexual self-care. HBM-based education can be recommended as a cost-effective method to achieve this goal, and it can be utilized by health professionals, including midwives and counselors, to enhance sexual self-care among these women. Conversely, if the results are not as expected, they could guide us in designing new strategies to improve sexual self-care. Additionally, this study will assess which HBM construct is the most significant and impactful in promoting sexual self-care, providing insights that can inform the content used in future programs and research.

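### The fallback for non-normal scores is the Friedman test, which has no arm term and so cannot compare intervention with control, and it conflicts with the sentence that assigns effectiveness to ANOVA

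*Protocol*

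**What the plan says.** The section on data management and analysis sets a rule by distribution. For the normal case, "For continuous variables with a normal distribution, ANOVA will be used between subjects"; for the other case, "for continuous variables without a normal distribution, the Friedman test will be employed". The next sentence reads: "The effectiveness of the intervention will be evaluated using ANOVA". It states no distribution condition and no model terms. The Abstract gives the methods in one line (data "will be analyzed through the ANOVA, Friedman test, and logistic regression modeling") and adds no two-group rank test.

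The rest of the protocol describes a between-arm question. The Abstract says "This is a randomized controlled trial with two parallel groups". The secondary objectives compare self-care scores and HBM items "in the intervention and control groups before, immediately after, and 8 weeks following the intervention". The sample size rests on a standardised effect of 0.7 for intervention against control. The primary outcome is the FSHS score, a 40-item Likert questionnaire. The secondary outcomes are HBM subscales of 3 to 8 five-point items each.

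**The concern.** The two halves of the rule are offered as alternatives for the same job, but they answer different questions. A between-subjects ANOVA asks whether the arms differ. Friedman asks whether scores differ across repeated measurements on the same women. Its usual counterpart is a one-way repeated-measures ANOVA, not a between-group one.

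The rule applies to continuous variables without exempting the outcomes, so as written it reaches the FSHS score and the HBM subscales. For a score sent to Friedman, a small p-value would show only that scores moved over time. Repeated questionnaires, clinic contact or time since diagnosis could produce such movement in both arms. The effectiveness sentence points the other way, so an analyst with a non-normal score could follow either sentence after seeing the data.

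**Working it through.** **1. What the trial is sized for.** Inputs from the Sample Size section: d = 0.7, z = 1.96 and 0.84. The standard formula for two independent means is n per group = 2(z₀.₉₇₅ + z₀.₈₀)²/d².

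2 × (1.96 + 0.84)² / 0.7² = 2 × 7.84 / 0.49 = 32.0

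This reproduces the protocol's 32 per group, so the trial is sized for a test of one arm against the other. (As printed, the formula has the 2 inside the square, which would give 64. That does not affect this point.)

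**2. What Friedman computes.** With N women and k time points, rank the k scores within each woman and let R_j be the rank sum at time j:

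χ² = 12 / [N k (k + 1)] × Σ R_j² − 3N(k + 1)

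With k = 3 and N = 64 (two arms of 32), this is Σ R_j² / 64 − 768. Arm appears nowhere in it. Adding a constant to all three scores of one woman leaves her ranks unchanged, so a constant difference between arms cannot move the statistic. In a numerical check with 64 simulated women, adding 5 units to every score in one arm left χ² = 1.906 and p = 0.386 unchanged.

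**3. What it rejects when the arms do not differ.** The protocol gives neither the correlation nor the time trend, so these are assumptions: no arm effect, three time points, latent within-woman correlation 0.5, 32 per arm, and the same rise in both arms from baseline to both later time points. Margins are normal, or exponential with SD 1 (joined by a normal copula). The second case matters because Friedman is triggered only by non-normal data. Rejection rates at the 5% level:

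| Common rise | Margins | Friedman, all 64 | Friedman, one arm of 32 | Mann-Whitney on change, between arms |
|---|---|---|---|---|
| none | normal | about 5% | about 5% | about 5% |
| 0.3 SD | normal | about 55% | about 28% | about 5% |
| 0.5 SD | normal | about 95% | about 67% | about 5% |
| 0.3 SD | exponential | about 92% | about 61% | about 5% |
| 0.5 SD | exponential | over 99% | about 92% | about 5% |

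The size depends on the assumptions. With exponential margins and latent correlation 0.6, for example, the pooled figure for a 0.3 SD rise is 96%.

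**4. Running Friedman in each arm does not repair it.** With no arm effect and a 0.3 SD common rise, the pattern of significant in the intervention arm but not in the control arm occurs in roughly 20% to 24% of trials across these settings. Contrasting two within-arm p-values is not a test of the difference between arms.

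**5. The two sentences side by side.** For a normal FSHS score, both lead to ANOVA. For a non-normal one, the first leads to Friedman and the second to ANOVA. Nothing in the protocol says which prevails.

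**The case against.** The strongest reply is the effectiveness sentence itself. It carries no normality condition and stands apart from the switching rule, which follows a sentence on reporting baseline characteristics. On that reading the arm comparison stays with ANOVA whatever the distribution, and Friedman describes change over the three time points. This reading is fair, and it limits what can be claimed. A reader might infer that the randomised comparison will certainly be lost once scores are non-normal. The text does not establish that; it follows only if the Friedman rule is applied to the outcome. What survives is the conflict: the rule exempts no outcome, and it names a within-woman test as the alternative to a between-subjects one.

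A reader might also infer from the Discussion, where "an increase in sexual self-care scores may indicate the effectiveness of this educational intervention", that success is defined by a before-after criterion. The sentence is hedged closing prose, not a decision rule, while the objectives and sample size both commit to comparing arms. It supports a wording suggestion only.

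Nor do the documents show that the trial would declare success with no difference between arms. That would need the FSHS score to fail a normality check that is not described, the effectiveness sentence to be set aside, and a time effect to be reported as a treatment effect. Nothing shows that a 40-item total will be non-normal, although the short HBM subscales are more exposed.

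Leaving detail to a statistical analysis plan does not answer the core point. The protocol names a specific test, and it is unsuitable for the place it is given.

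**Conclusion.** The point holds in this form. As a substitute for a between-subjects ANOVA, Friedman is the wrong test: it cannot compare intervention with control, and the protocol names no between-arm method for non-normal scores. The rule also conflicts with the effectiveness sentence for any non-normal FSHS or HBM score. These conclusions rest on the text and the form of the statistic and need no simulation.

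The consequence is conditional. If the Friedman rule is followed for an outcome, the randomised comparison of that outcome is not made. A common rise of 0.3 SD would then give a significant pooled result in more than half of trials without any arm effect, and in about nine in ten with strongly skewed scores. Those rates illustrate the direction and possible scale; they are not a forecast for this trial. Because the rule as written reaches the primary outcome, it should be corrected before analysis.

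**What to change.** In the data management and analysis section, and in the Abstract's list of methods, replace Friedman as the fallback with a prespecified between-arm method. Either of these would serve:

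- a between-arm rank method for non-normal scores, such as rank ANCOVA adjusted for the baseline score, or Mann-Whitney on change from baseline;
- one baseline-adjusted between-arm model (ANCOVA, with bootstrap or permutation inference if needed) used whatever the distribution, so that no switch is required. The protocol names no baseline covariate at present, so this would be an addition.

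Limit Friedman to describing change within each arm. Reword the effectiveness sentence so that it and the rule lead to the same analysis for every outcome. As a minor point, say in the Discussion that effectiveness means a difference between arms.

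The cost is protocol wording. Design, sample size and data collection are unchanged, and the methods are available in standard software.
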